### **10.2.2 Analytic Strategy by Specific Aim**

#### **10.2.2.1 Specific Aim 1**

To determine whether a punctuated six-month course of ARV therapy during treatment of active TB will delay HIV disease progression, as measured by time until CD4+ count falls below 250/ml, the rate of decline in CD4+ cell counts and the incidence of an AIDS-defining condition (Appendix II, WHO stage IV HIV infection or a definitive diagnosis of a severe bacterial infection that meets WHO Stage 3 classification ), among HIV-infected persons with active TB and CD4+ cell count above 350 cells/ml.

The analysis of this aim will be done in two stages. First, in an analysis of the randomized clinical trial, we will compare the rate of HIV disease progression, as measured by time until CD4+ count falls below 250/ml and the rate of decline in CD4+ cell counts, between TB patients randomized to receive either punctuated or anti-TB medications only with possible delayed ARV therapy using an intention-to-treat approach. All subjects randomized in the study will be analyzed according to the group to which they were assigned regardless of whether they remained adherent to the ARV treatment. This as-assigned analysis will fully preserve the benefits of randomized treatment allocation and will provide a conservative estimate of the benefit of the intervention. It represents the main analysis of the trial.

HIV Disease Progression when CD4+ count < 250/ml

The primary outcome for the study is HIV disease progression. This is defined as the time interval between enrollment and the development of one or more of the following endpoints, whichever occurs first: decline of CD4+ count < 250/µL, new AIDS-defining condition, or death. When a subject has met the criteria for primary outcome for CD4+ counts, the date for the first of 2 consecutive CD4+ counts will be used to mark failure time. The primary analysis of the study for each outcome will be to compare the failure-time distribution of the treated to the reference group. Separate failure-time distributions will be estimated for each treatment group using the Kaplan-Meier method78 and compared using the log-rank test.79 Stratified analysis will be performed for the primary outcome according to categories of baseline viral load.80 A Cox proportional hazards regression model81,82 will be developed to evaluate the effect of treatment on disease progression. In these analyses, the failure event will be HIV disease progression; subjects will be censored because of withdrawal during the study or at end of study. We will assess whether censoring is independent of study outcome as this is a fundamental assumption of survival analysis. In these regression models, observed event-free survival will be the dependent variable.

The basic Cox proportional hazards model for this analysis will be formulated as follows:

where h (t,X) is the observed hazard, h0 (t) is the baseline, unmeasured hazard for disease progression, β is the regression coefficient for treatment, ARV is the variable coding for immediate versus delayed ARV treatment (1 and 0, respectively), i the vector of regression coefficients for the covariates, Xi is the vector of covariates that may include time since treatment. This vector will contain known prognostic factors for HIV infection in Africa such as age, tuberculin skin test, baseline CD4+ count, hemoglobin, and performance status. This vector of covariates will also include the time period between initiating antituberculosis therapy and date of randomization to account for varying times in initiating antiretroviral therapy. The assumption of proportional hazards will be tested using graphical methods and formal statistical tests. If this assumption does not hold, then stratified Cox regression models will be developed, stratifying on the variable with non-proportional hazards.

The hazard ratio, or relative risk, for the comparison of immediate treatment versus delayed treatment will be estimated from the Cox regression model as:

where ARV (1) codes for immediate treatment and ARV (0) for delayed treatment. The likelihood ratio test using the –2 log-likelihood for nested models will be used to assess statistical significance. Confidence intervals (95%) for the hazard ratio will be calculated using the standard error of the regression coefficient.

In any clinical trial, non-adherence with the assigned treatment poses challenges not only in the conduct of the trial but in the analysis. Adherence with study medication will be optimized through health education, frequent monitoring and modified directly observed therapy during punctuated therapy. Despite these efforts, it is possible that non-adherence will occur. Non-adherent participants will remain in the analysis to preserve the strict intention-to-treat approach. To evaluate the potential impact of non-adherence, we will perform a stratified analysis for main outcomes according to level of non-adherence, as we have done in previous clinical trials.83,84

Although random allocation of treatment would balance known and unknown confounding factors at baseline between the punctuated ARV versus the reference arm, it is possible that losses during the first 6 months of observation will alter the nature or the study groups at the beginning of this observation period. To address this potential problem, the prognostic characteristics of the intervention and reference groups will be compared at the start of the post-intervention observation period. Failure-time methods that utilize the area under the survival curve or marginal structural models will be developed to adjust for any differences between these groups after the intervention period.

Rate of change in CD4+ count according to treatment periods

In addition to the main outcome, we will determine whether the study interventions alter the rate of decline in CD4+ counts by using a linear spline model with 2 time periods. The follow-up period will be divided into two periods: period 1 - from baseline until 6 months; period 2 - from 6 months until CD4+ count falls below 250/µL. Separate slope parameters will be fit for period 1 and period 2 using the linear spline model with a knot, t*, at 6 months. This approach will allow us 1) to analyze the magnitude of effect achieved during the punctuated treatment during period 1 and 2) to compare the rates of decline for the different treatment groups in period 2. The general model is given by:

where yij is the CD4+ count for subject i (i = 1,2, … n) and measurement j (j = 1, 2, … m), G represents the two mutually exclusive treatment groups (punctuated ARV vs. reference group), and t* = 6 months on study. Using appropriate contrasts, we can test for differences in **11G between the groups assigned to punctuated therapy or delayed therapy for period 1. In this analysis, the main interest is not whether there will be a difference in CD4+ slope between the treated and delayed group, but instead what is the magnitude of the difference. This information will be useful in analyzing the response during period 2. Again using appropriate contrasts, we will compare the slopes of the two treatment groups during period 2. The null hypothesis for this analysis is: **2Punct ARV = **2Delay ARV;; the alternative hypothesis is that the two groups will have different slopes in CD4+ measurement. To perform this analysis, we will use the linear mixed-effects model.85

where G represents the groups, as above, Zi is a design matrix containing time information, bi is a coefficient that captures random effects, ij are independent Gaussian random variables with mean = 0 and variance 2, t' = tj – (tj – t*), and (tj – t*)+ = 0 when tj  t*. This is an attractive model for this analysis because it can incorporate missing or mistimed observations, accommodate additional covariate terms, allow for trends in variance over time, and allow for separate analysis of time trends and separate slopes.86 In this analysis, we will evaluate a series of models to estimate and compare mean slopes in period 2 for each treatment combination. In this formulation of the model, the global test of the null hypothesis **5 = 0 will assess whether slopes differ among groups in period 2. As with all longitudinal studies, missing data represents a challenge in the analysis and may bias the estimates. During the conduct of the study, every effort will be made to minimize the missing information. At the time of analysis, the data will be evaluated to determine whether CD4+ counts are missing at random by comparing the distributions of missing information between groups over time. If results of this analysis show similar distributions, then we will assume that the CD4+ values are missing at random and analyze with likelihood-based methods to avoid bias.87 If this assumption is not tenable, then we will need to make additional assumptions regarding the pattern of missing information before proceeding with the analysis.

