## Inclusion

## Inclusion Criteria for Study Entry

Screening evaluations to determine eligibility must be completed within 14 days prior to study entry unless otherwise specified.

1. AFB Smear-positive or culture-positive, presumed pulmonary TB
2. Patients, male or female, aged 13-60 years
3. HIV seropositive (at any time)
4. CD4+ count > 350 cells/ml
5. Residence within 20 km of Kampala

6 Female study volunteers of reproductive potential (defined as girls who have reached menarche or women who have not been post-menopausal for at least 24 consecutive months, i.e. who have had menses within the preceding 24 months, or have not under-gone surgical sterilization (e.g. hysterectomy, bilateral oophorectomy, or salpingotomy) must have a negative serum or urine pregnancy test performed within 14 days prior to study entry.

1. If participating in activity that could lead to pregnancy, the female study volunteer must use a reliable method of contraception while receiving protocol-specified medication(s) and for 6 weeks after stopping the medications(s).
2. If the female volunteer is not of reproductive potential (girls who have not reached menarche, women who have been post-menopausal for at least 24 consecutive months, or women who have undergone surgical sterilization, salpingotomy) she is eligible without requiring the use of contraception.

7 Ability and willingness of subject or legal guardian to provide informed consent for study participation

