### **5.2.2 Randomization**

Treatment intervention will be randomly allocated to patients with active TB when patients enter Step 2 of the study. Eligible TB patients will be randomized with an allocation ratio of 1:1 to receive either punctuated ARV therapy or anti-TB treatment only with delayed ARV therapy. Randomization will be done with a permuted-block size of 16 to reduce the likelihood of unbalanced study arms in terms of size and prognostic factors. The assignment to study arm will be made by the UCSF data center to reduce the likelihood of inappropriate enrollment or treatment allocation.

Before the trial begins a list of computer-based random numbers will be generated using a pseudo-random number generator. These randomly allocated numbers will be used to assign eligible study patients to study arm. This list will be retained at the data center at UCSF. Once eligibility for study entry into Step 1 has been determined through the screening process, a form that contains a summary of study entry inclusion and exclusion criteria will be sent to the statistical center. Patients enter Step 1 where they are started on anti-TB treatment and monitored for contraindications to start the Trizivir-based ARV intervention regimen. All patients will be assessed beginning at week 1 and up to week 3 for contraindications to starting intervention. Upon determination of eligibility criteria for randomization, a form with criteria for randomization will be sent to the UCSF data center. Study entry and randomization criteria will be verified and a treatment assignment made according to the list of random numbers. Upon randomization, patients enter Step 2 of the study where they are initiated into study arm. Patients with contraindications for starting Trizivir-based punctuated ARV therapy without resolution during the 2 to 4 week period will be registered to Step 2, will not be randomized, will not be included in the primary analysis of the study, but will remain on study follow-up. They will be eligible for entry into Step 3 of the study, if during the study period, their CD4+ count drops 250/ml or an AIDS- defining condition develops as defined by WHO stage IV HIV infections or a definitive diagnosis of a severe bacterial infection that meets WHO Stage 3 classification (Appendix II).

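### The primary log-rank test carries no baseline CD4 stratum although the endpoint is mainly a CD4 threshold; the cost is power, of a size the protocol does not fix

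*Protocol*

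**What the plan says.** Under Specific Aim 1 (section 10.2.2.1), Kaplan-Meier curves are estimated for each arm and "compared using the log-rank test". No stratum is attached to that test. The next sentence is separate: "Stratified analysis will be performed for the primary outcome according to categories of baseline viral load". Viral load is the only stratifying factor named for the primary outcome, apart from level of non-adherence, which is not a baseline factor.

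The same section then sets out a Cox model for the same outcome. Its covariates are known prognostic factors "such as age, tuberculin skin test, baseline CD4+ count, hemoglobin, and performance status". The hazard ratio and its 95% confidence interval come from this model, and a likelihood ratio test "for nested models will be used to assess statistical significance". The protocol does not call the Cox model secondary.

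Allocation gives no help with CD4. Section 5.2.2 says "Randomization will be done with a permuted-block size of 16" and names no stratification factor. Entry requires "CD4+ count > 350 cells/ml" with no upper limit. Screening CD4 is measured in every patient (sections 4.5 and 7.1). Section 1.1.2 grants that higher HIV RNA goes with faster CD4 decline but ranks the CD4 level above it as a predictor of progression.

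**The concern.** The main component of the endpoint is a fixed threshold on the variable that also decides entry. A patient entering just above 350 has about 100 cells to lose, while one entering at 800 has 550. Starting distance from the threshold is therefore built into the failure time. A log-rank test that pools these patients spreads the treatment comparison over a large, known and measured source of variation, and that costs power when the treatment effect acts within CD4 levels.

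The plan also leaves two significance tests on one endpoint: a log-rank that does not use CD4 and a Cox likelihood ratio test that does. Section 10.3.1 refers only to a standardized test statistic for the main outcome, to be compared with the boundaries of Table 10. It does not say which of the two that is.

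**Working it through.** **How far starting CD4 moves the failure time.** Section 10.1 expects a decline of 7 to 10 cells/month in the reference arm. Time to 250 is (entry CD4 - 250) / slope.

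| Entry CD4 | At 10/month | At 7/month |
|---|---|---|
| 351 | 101/10 = 10 months | 101/7 = 14 months |
| 500 | 250/10 = 25 months | 250/7 = 36 months |
| 600 | 350/10 = 35 months | 350/7 = 50 months |
| 800 | 550/10 = 55 months | 550/7 = 79 months |

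These are mean slopes applied to single patients, so they show a strong effect but not its share of the total variation. In a linear-decline model with mean slope 8.5 cells/month, baseline CD4 explained 38-54% of the variance of log time when the slope had a coefficient of variation of 0.5. It explained only 10-17% when that coefficient was 1.0. Both coefficients are assumptions.

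**The plan's own power.** Inputs from section 10.1 and the synopsis: 175 per arm, effect size 35% (taken as hazard ratio 0.65), two-sided alpha 0.05, 3-year accrual, 5% dropout per year, constant hazard, 5 years in total. With hazard λ, dropout rate η = -ln(0.95) and s = λ + η, the probability of an observed event is (λ/s) × [1 - (e^(-2s) - e^(-5s)) / (3s)]. Schoenfeld power is Φ(½ √d × |ln 0.65| - 1.96), where d is the expected number of events.

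- 50% progression at 2 years: λ = ln 2/2 in the reference arm and 0.65 times that in the punctuated arm. d ≈ 199, and Φ(½ × 14.1 × 0.431 - 1.96) = 86%, against 90% stated.
- 50% at 3 years: d ≈ 153, and Φ(½ × 12.4 × 0.431 - 1.96) = 76%, against 80% stated.

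The stated figures are not matched exactly. That is a separate matter, and the comparison below does not depend on it.

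**What stratifying by CD4 changes.** Same accrual, dropout and follow-up, 175 per arm, hazard ratio 0.65 conditional on CD4, 2,000 simulated trials per row. The documents give no prognostic strength for CD4, so it is varied as an assumed hazard ratio per 1 SD lower CD4. Power is for the unstratified log-rank versus the log-rank stratified by CD4 quartile.

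| Assumed HR per SD | 50% at 2 years | Change | 50% at 3 years | Change |
|---|---|---|---|---|
| 1.0 (none) | 85% vs 84% | -1 | 75% vs 75% | 0 |
| 1.65 | 79% vs 84% | +5 | 70% vs 73% | +3 |
| 2.2 | 70% vs 82% | +12 | 62% vs 72% | +10 |
| 3.0 | 57% vs 78% | +21 | 53% vs 71% | +18 |

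At 70% power the 95% Monte Carlo margin is 1.96 × √(0.7 × 0.3/2000) = ±2 points, so -1 to 0 means no detectable cost.

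**Validity.** With no treatment effect and an assumed hazard ratio of 2.2 per SD, the rejection rates were 5.6% unstratified and 5.5% stratified. The margin is 1.96 × √(0.05 × 0.95/2000) = ±1 point, so both agree with 5%.

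**Tuberculin skin test.** It is one of the example covariates but appears in no evaluation list: not in screening (4.5, 7.1), Step 1 (5.1, 7.2), Step 2 (7.3), Step 3 (7.4), sick visits (7.5) or the Appendix I tables. CD4, hemoglobin (from the blood count) and Karnofsky score are obtained at screening.

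**The case against.** The strongest reply is that CD4 is already in the plan. The Cox model sits under the same aim, for the same endpoint, lists baseline CD4, and yields the hazard ratio, its interval and a test. That stands. A reader might infer that the primary analysis ignores CD4 altogether, or that the log-rank itself is stratified on viral load instead. Neither follows from the text: CD4 is in the Cox model, and the viral-load analysis is a separate sentence.

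Second, an unstratified log-rank after unstratified 1:1 blocked randomization is a standard, valid test. Its type I error already allows for chance imbalance in CD4. That also stands, so a claim of bias would be wrong.

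Third, section 10.1 defines the effect size from the hazards of the two groups as wholes and powers the matching unstratified test. If 0.65 is the marginal hazard ratio, no shortfall against the plan's own power is shown. The table instead shows what is gained if 0.65 holds within CD4 levels.

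Fourth, one might read the tuberculin entry as making the listed model impossible to fit. The list is introduced as examples, and the model can be fitted without that item.

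What the reply does not remove is that the log-rank leaves out a strongly prognostic value already measured in every patient, and that two tests compete for one endpoint.

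**Conclusion.** The point holds as a matter of efficiency and of naming one test. The log-rank carries no CD4 stratum, the only baseline stratifier named for the primary outcome is viral load, and CD4 enters only through the Cox model. In the simulations the gain from using CD4 runs from nothing detectable to 21 points, and it is 3 points or more once CD4 is assumed prognostic at 1.65 per SD. The size rests on the assumed prognostic strength of CD4 and on a constant conditional hazard ratio of 0.65. The documents fix neither, so there is no single corrected power figure.

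It would be tempting to call CD4 the dominant determinant of the outcome. The protocol's slopes support a strong effect, but dominance depends on between-patient variation in slope, which the protocol does not give. AIDS-defining conditions and death also count as events. The tuberculin skin test is a real but minor inconsistency.

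**What to change.** In section 10.2.2.1, before any comparative look, name one primary test. It can be a log-rank stratified by prespecified screening-CD4 categories (for example quartiles), or the Cox test of treatment adjusted for log screening CD4. State in section 10.3.1 that the same statistic is compared with the interim boundaries. Keep the unstratified log-rank and the Kaplan-Meier curves as supportive. Report both the conditional and the marginal hazard ratio, because they estimate different quantities.

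Remove tuberculin skin test from the covariate examples. Baseline log HIV RNA, which is collected at the Step 1 and Step 2 baselines, can take its place.

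The cost is wording only: no extra visit, sample or patient. If CD4 turned out not to be prognostic, the simulations show a loss of at most about one point of power.

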**5.0 STUDY PHASES: STUDY ENTRY, INTERVENTION AND POST-OUTCOME**

##

## 5.1 Study Entry – Step 1

All patients in this study will receive routine treatment for tuberculosis (see Section 5.1.1). The experimental intervention in this study is the use of punctuated antiretroviral therapy for six months during treatment for tuberculosis. Because standard anti-TB drugs represent the background treatment, these drugs will not be considered study drugs. When patients have been found to be eligible for the study and have given informed consent, all patients will be started on antituberculosis treatment, given daily for a total of six months and will have the following baseline assessment:

1. Informed consent for study
2. Medical history and physical examination, including weight
3. HIV RNA Roche Amplicor
4. PBMC storage/ immune function (Flow cytometry to assess cell surface activation markers, EliSpot to assess CD4 and CD8 T cell specificity to HIV and microbial peptides, Whole blood assays to determine antigen specific response to HIV and microbial antigens)
5. Plasma & Buffy Coat storage

Patients will be evaluated weekly while in Step 1. At one week from study entry all patients will be assessed for readiness to start on the Trizivir-based punctuated ARV therapy with the following evaluation:

1. Medical history and physical examination, including weight
2. New Diagnosis and hospitalization survey
3. Adverse event survey
4. Pregnancy test (urine or serum *β*-HCG)
5. Complete blood count with differential
6. Liver function tests (AST and serum bilirubin)
7. Serum creatinine
8. Adherence to antituberculosis therapy
9. Quality of life survey
10. Disease specific diagnostic tests

The patient will be scheduled to return to the clinic 1 week after this evaluation (two weeks after the start of TB therapy) to be randomized or identified as having contraindications (see Section 4.4). If the patient has contraindications to starting the Trizivir-based ARV intervention they will be scheduled to return to the clinic in another week (Week 3) and be reassessed.

Thus, all patients evaluated at week 1 will be scheduled to return to the clinic at week 2, and may be randomized or reassessed for randomization at that time; those patients that have contraindications at week 2 may be scheduled to return to the clinic for randomized or reassessment at week 3; and those patients reassessed at week 3 will be scheduled to return to the clinic and may be randomized at week 4.

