### **5.2.1 Punctuated Antiretroviral Therapy**

#### **5.2.1.1 Drug Regimens, Administration and Duration**

Table 4. Study Intervention

| Study Arm | N | Intervention Period | Post-Outcome |
| --- | --- | --- | --- |
| Punctuated Therapy | 175 | 2RHZE/4RH QD + 6 Months ABC/3TC/ZDV (as Trizivir®) BID | Delayed antiretroviral therapy* |
| Delayed Therapy | 175 | 2RHZE/4RH QD | Delayed antiretroviral therapy* |
| *ARVs will be offered during study period to any patient when CD4+ count falls below 250/µL or when an AIDS-defining condition occurs. Patients who do not develop a primary study outcome during the study period will not be offered delayed ARV therapy. | | | |

Punctuated Therapy Arm:

Patients enrolled in the punctuated therapy arm will receive oral abacavir 300 mg/ lamivudine 150 mg/zidovudine 300 mg (as Trizivir®) twice daily with or without food. As each subject is enrolled, the study site must ensure that (1) the subject receives the **Trizivir**®warning card and medication guide, (2) the designated health care provider (e.g., physician, study nurse coordinator, or pharmacist) reviews the signs and symptoms of a hypersensitivity reaction (HSR) with the subject, and (3) the subject verbalizes an understanding of the steps to take in the event of a suspected HSR, including when and how to contact the study physicians. Study physicians will be available 24 hours per day through office or cellular telephone. Individual medication components of Trizivir®, will be available for dose adjustment.

For subjects who start Trizivir® but are found to be intolerant of it, alternative regimens will be available as described in Section 5.2.1.4, Antiretroviral Drug Substitutions and Replacements.

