### **7.3.2 Intervention Phase Study Visit**

Following treatment assignment and initiation of study intervention, patients will be evaluated one and two weeks after initiation of ARV treatment and then monthly during study intervention phase (see Appendix I, Step 2).

1. Medical history and physical examination including weight, major TB and HIV-related signs and symptoms and primary study outcomes (Week, 2, Months 1, 2, 3, 4, 5, 6, and as indicated)
2. New diagnoses and/or hospitalizations since the last study visit (Week 2, Months 1, 2, 3, 4, 5, 6, and as indicated)
3. Posterior-anterior chest X-ray (8 weeks, and between 22 and 24 weeks)
4. Adverse experiences survey (Week 2, months 1, 2, 3, 4, 5, 6, and as indicated)
5. Sputum semi-quantitative AFB smear and culture on solid media X 2 (between 4 & 6 weeks, 8 weeks, and between weeks 18 & 20 from the start of anti-TB treatment)
6. MTB drug susceptibility (as clinically indicated)
7. Urine or serum -HCG pregnancy test (females of child bearing potential only) (Week 2, Months 1, 2, 3, 4, 5, 6, and as indicated)
8. CBC, differential white blood cell and platelet count (Week 2, Months 1, 2, 3, 6, and as indicated)
9. Serum aspartate aminotransferase (AST), serum total bilirubin (Week 2, Months 1, 2, 3, 6, and as indicated)
10. Serum creatinine (as clinically indicated)
11. CD4+ lymphocyte counts (Weeks 2, Months 1, 3, 6, and as clinically indicated)
12. Plasma HIV RNA by Roche Amplicor (Weeks 2, Months 3 and 6, and as clinically indicated)
13. Adherence Questionnaire for antituberculosis and antiretroviral therapy (Week 2, Months 1, 2, 3, 4, 5, 6, and as indicated)
14. Quality of life assessment (month 6)
15. Urine INH testing (Week 2, Months 1, 2, 3, 4, 5, 6)
16. Plasma storage (Weeks 1, 2, Months 1, 2, 3 and 6)
17. PBMC storage/ immune function (Week 2, Months 3, and 6)
18. Store MTB isolate for DNA fingerprinting (All isolates from positive cultures of suspected relapse cases will be stored at -70° C for DNA finger printing with the patient’s initial isolate, as clinically indicated)
19. Disease specific diagnostic test (as clinically indicated)

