#### **10.2.2.4** **Additional Analyses**

The primary analysis as described will be performed according to the principles of intention to treat. In the event of withdrawal secondary to ineligibility, non-adherence, refusal, or toxicity, we will perform subgroup analyses of patients as treated, stratified by the degree of adherence. Propensity scores will be generated to capture the likelihood of non-adherence. Using the propensity scores, we will stratify patients according to the scores and examine the effect within and across strata. If the results of this ancillary analysis concur with the intention-to-treat analysis, then the interpretation of the results will be straightforward. If the results of this analysis differ from the intention-to-treat analysis, then the intention-to-treat analysis will be reported as the primary results because it is least likely to be biased.

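### Supportive analyses by observed ARV adherence cannot be stratified alike in both arms, so they can show a spurious adherence gradient if adherence is related to prognosis

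*Protocol*

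**What the plan says.** Section 10.2.2.1 makes intention to treat the main analysis, with patients analysed as assigned "regardless of whether they remained adherent to the ARV treatment". It then turns to non-adherence: "Adherence with study medication will be optimized through health education, frequent monitoring and modified directly observed therapy during punctuated therapy". To gauge the effect of any non-adherence that remains, "we will perform a stratified analysis for main outcomes according to level of non-adherence".

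Section 10.2.2.4 returns to the subject. If patients withdraw for ineligibility, non-adherence, refusal or toxicity, "we will perform subgroup analyses of patients as treated, stratified by the degree of adherence". It also plans a propensity score for non-adherence, with the effect examined within and across strata of that score. Agreement with intention to treat is taken to make interpretation simple. If the results disagree, intention to treat is reported as primary.

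Two other places settle which treatment has an adherence level. Section 5.1 says of the anti-TB regimen: "Because standard anti-TB drugs represent the background treatment, these drugs will not be considered study drugs". Table 4 in section 5.2.1.1 gives the control arm's treatment in the intervention period as "Delayed Therapy | 175 | 2RHZE/4RH QD", with no ARV until an outcome.

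**The concern.** Adherence is a behaviour observed after randomisation. If the stratifier is adherence to the punctuated ARV course, a delayed-arm patient has no value for it before the outcome. What can be compared is a self-selected part of the punctuated arm with the delayed arm as a whole. If patients who take their ARV reliably have a better prognosis anyway, they look better than the delayed arm, and those who do not look worse, whatever the drug does.

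The protocol makes such a link plausible but does not establish it. Hemoglobin and performance status are listed in section 10.2.2.1 as prognostic factors, while section 8.1.2.2.2 allows ZDV to be interrupted or replaced for anemia. Section 10.2.2.4 groups toxicity and refusal with non-adherence.

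At stake is the reading of the trial, not its primary test. A biased supportive analysis can lend false support to a chance-positive intention-to-treat result, or suggest that a null result was a failure of adherence.

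**Working it through.** The protocol states no figure for this analysis, so there is none to reproduce. The check has two parts.

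**1. Which adherence is meant**

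- Section 10.2.2.1 speaks of study medication during punctuated therapy, and of adherence to ARV.
- Section 5.1 excludes anti-TB drugs from the study drugs.
- Table 4 gives the delayed arm (175 patients) anti-TB drugs only before an outcome.
- Section 7.3.2 schedules an "Adherence Questionnaire for antituberculosis and antiretroviral therapy" at Week 2 and Months 1 to 6. Anti-TB adherence is therefore recorded in both arms, but neither analysis section names it as the stratifier.

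ARV adherence is thus the natural reading, and it has no counterpart in the delayed arm.

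**2. Size of the gradient when the drug does nothing**

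Assumptions, none of them protocol figures: a binary prognostic factor with 50% prevalence and hazard ratio θ; the factor triples the odds of ARV non-adherence; a share q of 10% to 30% of the punctuated arm is non-adherent. The non-adherent stratum would then hold 0.10 × 175 to 0.30 × 175, about 18 to 53 patients.

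Let p0 and p1 be the non-adherence probabilities in good- and poor-prognosis patients:

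- p0 + p1 = 2q and p1/(1 − p1) = 3·p0/(1 − p0).
- For q = 0.20 this becomes 2p0² + 3.2p0 − 0.4 = 0, so p0 = 0.1165 and p1 = 0.2835.
- Poor-prognosis share: non-adherent 0.2835/0.40 = 0.709; adherent (1 − 0.2835)/1.60 = 0.448; whole delayed arm 0.50.
- Mean initial hazard relative to a good-prognosis patient is 1 + (θ − 1) × share. With θ = 2, non-adherent against delayed is 1.709/1.5 = 1.14, and adherent against delayed is 1.448/1.5 = 0.97.

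A simulation with 200,000 patients per arm and Cox estimates over follow-up gives the same 1.14 and 0.97 for this case. Over q = 10% to 30%, with a true hazard ratio of 1.00:

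| θ | Adherent vs whole delayed arm | Non-adherent vs whole delayed arm |
|---|---|---|
| 1 (no link) | about 1.00 | about 1.00 |
| 1.5 | 0.97–0.99 | 1.07–1.09 |
| 2 | 0.94–0.98 | 1.12–1.17 |
| 3 | 0.92–0.97 | 1.21–1.26 |

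With a uniform true hazard ratio of 0.65 and θ = 2, the strata show 0.63–0.66 (adherent) and 0.75–0.79 (non-adherent): an apparent dose-response where none exists.

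When the same latent adherence type is compared in both arms under no drug effect, the hazard ratios return to 0.98–1.01 in every scenario.

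**Sensitivity to a stronger link.** Assumptions: 175 per arm, 3-year accrual, 5 years in total, 5% yearly dropout, about 80% adherent, gamma frailty variance 0.5 to 1.0, adherence odds changing 1.5- to 3-fold per standard deviation of frailty. Under no drug effect, adherent patients against the whole delayed arm give 0.84–0.96, with p < 0.05 in 5% to 18% of trials. Non-adherent patients give 1.25–2.09, with p < 0.05 in 15% to 76%. With no link the hazard ratios are 1.00–1.02 and the error rates 4% to 6%.

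**The case against.** The other side has several fair points.

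- **The stratifier is not fully specified.** Section 10.2.2.1 opens with departure from assigned treatment, which both arms have. Section 5.2.4 applies observed therapy to anti-TB drugs and ARV alike and links it to adherence with study medication, so usage is not uniform. Anti-TB adherence could be classified in both arms. It is not named, however, and it would still be a post-randomisation variable that the assigned arm could affect. The comparator is not named either; the whole delayed arm is what remains if the strata rest on ARV adherence.
- **Detail may sit in the SAP or in the earlier trials cited for the method.** That would cover cut-points. It would not cure a named stratifier that one arm cannot have.
- **Propensity strata are already planned.** This stands, and it makes the repair small. The text does not say that the score is built from baseline data in the punctuated arm and carried over to the delayed arm, and it leaves the as-treated subgroups in place.
- **Intention to treat prevails if results differ.** This also stands, and no stopping boundary depends on these analyses.

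A reader might infer that these analyses will show benefit in adherers and harm in non-adherers even if ARV does nothing. The documents do not support that. The gradient needs a link between adherence and prognosis, for which the protocol gives no figure. Observed dosing six days a week also aims to keep non-adherence low.

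**Conclusion.** The point holds as a flaw in supportive analyses. On the protocol's own definitions, strata of observed ARV adherence cannot be formed alike in both arms. The comparison is therefore not randomised and can show a spurious gradient.

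Under the moderate assumed links the distortion is modest: up to 8% in the adherent hazard ratio and up to 26% in the non-adherent one. Under the stronger frailty assumptions it is larger, and it is nil if adherence and prognosis are unrelated. All of these sizes rest on assumed links and assumed non-adherence rates.

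The primary conclusion is not at risk, and it would be wrong to infer that it is. The change is still worth making, because section 10.2.2.4 treats agreement with these analyses as simplifying the interpretation of the intention-to-treat result, and a biased check can agree or disagree for the wrong reason.

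**What to change.** In sections 10.2.2.1 and 10.2.2.4, replace the observed-adherence strata and the as-treated subgroups with the propensity strata already planned. State three things:

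1. The adherence measure and the period it covers.
2. The non-adherence score is fitted in the punctuated arm on baseline covariates only, and the fitted score is then given to every patient in both arms.
3. The randomised arms are compared within strata of that score.

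A complier-average effect with randomisation as the instrument is an option. Observed adherence may still be reported descriptively within the punctuated arm. The precedence of intention to treat stays as it is.

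The cost is analysis wording; no new data are needed. The intervals will be wider and a modelling assumption has to be stated. With perhaps 18 to 53 non-adherent patients to fit the score on, the covariate list should be short. The strata will describe patients likely to adhere, not those who did.
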